### Psychosocial and other non-physical harms substudy

A subset of approximately 500 participants consisting of all those who have an abnormal CT scan report (YKST 2–5) between March 2022 and October 2022 and a random sample of one-third of those with normal scans (YKST 1) recruited within the same time period will be sent a short questionnaire 3 months and 6 months after the scan to evaluate outcomes in relation to psychological, social and financial harms and dissatisfaction with healthcare. Questionnaires will be sent by post, with participants having the option to complete the questionnaire online and one reminder will be sent 2 weeks after each questionnaire to reduce non-response bias. The questionnaire will include validated measures where possible, including the Psychological Consequences Questionnaire (PCQ),^20^ the Short form of the Spielberger State Trait Anxiety Inventory (STAI),^21^ the EQ-5D-5L^22^ and a single question asking how participants would rate their general health now compared with before they were invited to take part in YKST. The financial consequences of having the scan will be measured using five questions from a previous study^19^ and satisfaction with healthcare using the abbreviated measure to assess trust in the medical profession.^23^ The questionnaire will also assess participant satisfaction with the information they received and whether they felt they had had sufficient time and information to make the decision whether or not to accept the scan.

### Withdrawal of consent

If participants wish to withdraw from the study, no further data will be collected on them, though we will keep all data collected to that point. All patient withdrawals will be recorded.

### Safety

Adverse events occurring between the time the participants enter the mobile van for their T2 visit and the time that their final result letter is written to them and they are discharged from the study will be recorded and reported in line with Good Clinical Practice.

### Sample size

The maximum sample size is limited to those participants who attend for their YLST T2 visit. Approximately 6500 participants were recruited into YLST and it is estimated that 80% of those will attend for the T2 visit. Recruitment began 2 months into T2 on 10 May 2021 and will run until 31 October 2022. Approximately 4700 individuals will therefore be eligible for inclusion into YKST. If 80%–90% of those take up the additional screening, it will be possible to measure the proportion taking up the additional scan, the primary quantitative outcome of this study, to within 1%. For the qualitative substudy, the principles of information power^24^ will be used to decide when to cease data collection but we anticipate interviewing up to 40 participants. We will purposefully sample participants with the aim to include approximately 20 who accept the additional scan and 20 who do not, with a range of ages, sex, ethnicity and socioeconomic status. For the qualitative interviews with healthcare professionals, there are approximately 10 closely involved in the screening process and all will be approached.

### Data analysis

#### Primary outcomes

We will report the proportion of the population attending the T2 screening round who (1) are eligible to take part in YKST; (2) are invited to take part in YKST; (3) consent to the additional scan within YKST and (4) decline taking part in YKST. We will also report these proportions by age, sex, smoking status, ethnicity and socioeconomic status and compare those invited who accept and undergo the abdominal CT scan between demographic subgroups. The additional time required at each stage (obtaining consent, performing, reporting and reviewing the scans and feeding back the results to participants) of the combined screening approach will be reported. Qualitative data evaluating the acceptability of the combined screening approach will be analysed using Framework analysis, guided by the Theoretical Framework of Acceptability.^18^ Each transcript will be read by at least two members of the study team with other members of the study team reading some of the transcripts and contributing to discussions about the overall findings.

#### Secondary outcomes

Descriptive summaries of secondary outcomes will be reported. All clinical outcomes will be based on the final diagnosis obtained from the 6-month follow-up data. When reporting the prevalence and stage distribution of RCC, we will present data among the participants who had the abdominal CT as well as among those from the baseline round of scanning in YLST who either had a renal mass identified in that baseline (T0) lung LDCT or staging investigations for any lung lesions identified and so would have had their full kidneys imaged.

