## Objectives

The primary study objectives are as follows:

To quantify the uptake of non-contrast abdominal CT to screen for RCC and other abdominal pathology as part of a combined screening modality with thoracic LDCT within a lung health check.To assess the acceptability to patients of combined lung and RCC screening by non-contrast CT scanning.To evaluate the logistics and acceptability to healthcare professionals involved in the combined lung and RCC screening pathway.To pilot the majority of procedures for a subsequent full-scale randomised controlled trial of RCC screening by non-contrast CT scanning within lung cancer screening.

The secondary study objectives are to estimate:

The prevalence of renal masses and RCC found on non-contrast CT screening in an appropriate age (55–80 years) and risk group (smokers and ex-smokers).The stage distribution of RCC identified through non-contrast CT screening.The prevalence of incidental renal findings on non-contrast CT scanning.The prevalence of non-renal findings on non-contrast CT scanning.The incidence of RCC in the upper pole of the kidney over sequential non-contrast CT scans.

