## Outcome measures

The primary outcome measures are:

The proportion of individuals invited to have an additional abdominal CT while attending a second round of lung cancer screening who take up the offer of the abdominal CT.The acceptability to participants of combined lung and RCC screening by non-contrast CT scanning.The acceptability to healthcare professionals involved in the combined screening approach.The additional time required for the combined screening approach.

The secondary outcome measures are:

The proportion of participants found to have a renal mass or RCC to provide an estimate of the prevalence of RCC found on non-contrast CT screening in 55–80 years smokers and ex-smokers.The stage distribution of RCC identified through non-contrast CT screening.The proportion of participants found to have incidental renal findings on non-contrast CT scanning.The proportion of participants with non-renal findings on non-contrast CT scanningThe proportion of RCCs found on the upper pole of participants at the second thoracic screening round who did not have them in the baseline round, to estimate the incidence of RCC over sequential non-contrast CT scans.

Data will also be collected on further investigations, procedures and management of findings identified on abdominal CT to estimate the individual and health system burden of incidental findings and on the agreement of radiologists reporting the scans and the abdominal CT scan dose and quality to assess the safety. We will also collect long-term (10-year) follow-up data on RCC and other abdominal pathology and apply for CAG approval to obtain data on RCC among participants within YLST who were not invited to take part in YKST.

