**Figure 1 F1:**
[figure not shown]
Study recruitment. GP, general practice; LDCT, low-dose CT; LLP, Liverpool Lung Project; PLCO, Prostate, Lung, Colorectal and Ovarian; USPSTF, US Preventive Services Task Force; YKST, Yorkshire Kidney Screening Trial; YLST, Yorkshire Lung Screening Trial.

Eligibility for YLST is detailed in figure 1. All those not diagnosed with lung cancer or any other metastatic cancer following the YLST baseline visit (T0) are invited back for T2 between May 2021 and October 2022. The exclusion criteria for YKST at that point are as follows:

Abdominal or thoracic CT within the last 6 months.Unable to have an abdominal or thoracic LDCT.Previous diagnosis of RCC.Unable to provide informed consent.

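### RCC prevalence is to be presented in a T0 group entered partly by having a renal mass, so that proportion is conditioned on the outcome and is not a population estimate

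*Protocol article*

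**What the plan says.** The analysis rule is in the Secondary outcomes part of Data analysis. It begins "When reporting the prevalence and stage distribution of RCC, we will present data among the participants who had the abdominal CT as well as" and then names a second group from the baseline (T0) lung scan. There are two ways into that group:

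- a renal mass seen on the T0 thoracic LDCT ("among those from the baseline round of scanning in YLST who either had a renal mass identified in that baseline (T0) lung LDCT");
- a staging work-up for a lung lesion ("or staging investigations for any lung lesions identified and so would have had their full kidneys imaged").

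Outcome measures defines the quantity of interest: "The proportion of participants found to have a renal mass or RCC to provide an estimate of the prevalence of RCC" in smokers and ex-smokers aged 55–80. The matching stage objective is "The stage distribution of RCC identified through non-contrast CT screening". The YKST exclusion criteria include "Previous diagnosis of RCC", so an RCC diagnosed after T0 cannot appear among the abdominal-CT participants. The Introduction states that the thoracic LDCT covers only the upper pole of the kidneys.

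The protocol does not say whether the T0 group is shown separately or pooled with the abdominal-CT participants.

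**The concern.** Bringing in T0 cases makes sense, because the exclusion criterion removes them from YKST. The difficulty is the group in which they are counted. Entry by the first route requires a renal mass, which is itself part of the outcome. Within that route, the proportion with RCC is the positive predictive value of a mass seen on LDCT, not a prevalence. People whose upper poles were imaged at T0 and showed nothing drop out of the denominator, unless they happened to be staged for a lung lesion.

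The stated reason for the restriction, complete kidney imaging, does not remove this selection: in the first route the complete imaging happens because a mass was seen.

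The estimates are meant to inform a health economic analysis and later randomised trials. Few RCCs are expected at T2, so a handful of T0 cases over the wrong denominator can visibly shift the reported figure.

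**Working it through.** **Plan's own figure.** The protocol gives none for the T0 group, so there is nothing to reproduce on this point. One input can be checked. Of about 6500 recruited, 80% attending T2 gives 5200. Recruitment began two months into T2 and ran about 18 months. With steady attendance and T2 ending when recruitment ends (assumptions), 5200 × 18/20 = 4680, which agrees with the stated 4700.

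**Inputs from the protocol**
- N0: "Approximately 6500 participants were recruited into YLST" (Sample size). The number actually scanned at T0 is not stated.
- T2: "Approximately 4700 individuals will therefore be eligible for inclusion into YKST". Uptake of 80–90% gives 3760–4230 scans; 4230 is used below.
- p, true prevalence: 0.21% (general population, Introduction) or 0.5% (5 per 1000, Invitation process).

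**Assumptions, because the protocol gives no values**
- f, share of RCCs visible as a mass on the T0 LDCT: 25–50%.
- PPV, share of such masses that are RCC: 20–80%.
- s, number with a staging work-up: 65–390 (1–6% of 6500).

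**Formulas**
- T0 group as its own denominator: (6500pf + sp) / (6500pf/PPV + s).
- Inflation, after dividing by p: (6500f + s) / (6500pf/PPV + s).
- All T0-scanned as denominator: (6500pf + sp) / 6500.
- Pooled: add 4230 scans to the denominator of the T0 group. Add 4230p cases to its numerator, or 4230p(1 − f) cases if RCCs detected at T0 have left the T2 population.

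**One case in full** (p = 0.21%, f = 25%, PPV = 50%, s = 195)
- Mass route: 6500 × 0.0021 × 0.25 = 3.41 RCCs among 3.41/0.5 = 6.8 people.
- Staging route: 195 × 0.0021 = 0.41 RCCs among 195 people.
- Own denominator: 3.82/201.8 = 1.89%, which is 9.0 times p.
- All T0-scanned: 3.82/6500 = 0.059%, which is 0.28 times p.
- Pooled: (8.88 + 3.82)/(4230 + 201.8) = 0.287%, which is 1.37 times p.
- Pooled, T0 cases removed before T2: (6.66 + 3.82)/4431.8 = 0.237%, which is 1.13 times p.

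**Full ranges over the assumptions**

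| Handling of T0 data | p = 0.21% | p = 0.5% | Ratio to p |
|---|---|---|---|
| T0 group as own denominator | 1.0–9.5% | 2.3–19.4% | 4.7–45 |
| Pooled with 4230 T2 scans | 0.28–0.37% | 0.67–0.87% | 1.34–1.75 |
| Pooled, T0 cases removed before T2 | – | – | 1.11–1.26 |
| All 6500 as T0 denominator | 0.05–0.12% | 0.13–0.28% | 0.26–0.56 |

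**When would the first row be harmless?** If masses are few relative to s, inflation is about 1 + 6500f/s. It falls below 2 only when s exceeds 6500f, which is 1625 people at f = 25%, a quarter of the cohort.

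**Expected T2 cases.** 3760–4230 scans give about 8–9 RCCs at 0.21%, or 19–21 at 0.5%.

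**Combined first-screen figure.** Take d0 = 6 T0 cases (assumed) in N0 = 6500, and d2 = 8.4 in N2 = 3995 (0.21% at 85% uptake). Then d0/N0 + (1 − d0/N0) × d2/N2 = 0.092% + 0.9991 × 0.210% = 0.30%. Pooling the same cases with a selected group of 300 (assumed) gives 14.4/4295 = 0.34%, about 1.1 times as large.

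**The case against.** The best defence is that the sentence only promises to present data in both groups. It does not say that a T0 proportion will be offered as population prevalence. The T0 cases may be meant simply to restore those lost to the exclusion criterion, and the abdominal-CT prevalence is reported as well. The outcome is secondary and descriptive, the study is a feasibility study, and the Discussion concedes that it is too small for precise prevalence. A denominator detail might sit in the full protocol or SAP.

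Part of this stands. The abdominal-CT figure is sound if kept apart, and the primary outcomes are untouched. But the sentence covers prevalence explicitly and fixes the T0 group by its entry routes, so this is a stated rule and not a missing detail. The conceded imprecision is random error, not this bias.

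Four stronger inferences are tempting, and the documents do not support them:

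- *The reported prevalence will be inflated many-fold.* Dividing 6500 by an assumed group of 100 to 300 gives 65 to 22, but the group size is not in the protocol. Multiples of that order need the T0 group to stand as its own denominator; under pooling the effect is below two-fold.
- *T0 RCCs over 6500 is the true prevalence.* It is a lower bound, because only the upper poles are imaged.
- *Both entry routes select on RCC.* The staging route selects on lung lesions, which limits representativeness only.
- *The stage distribution shares the denominator fault.* Stage is distributed among cases, so it does not. The remaining question there is how each case was detected.

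**Conclusion.** The point holds for the T0 prevalence. As written, it is conditioned on a finding that belongs to the outcome, and it cannot be read as prevalence in smokers and ex-smokers aged 55–80. Its size cannot be fixed from the protocol. It is several-fold or more (4.7 to 45 over the assumed f, PPV and s) if the T0 group is its own denominator, and roughly 1.1- to 1.75-fold if pooled. That the bias is upward is secure; the multiples are only as good as the assumptions. For stage, the point is limited to labelling: RCCs found only on lung-lesion staging were not found by the screening route that the objective names.

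**What to change.** Amend the Secondary outcomes paragraph as follows:

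1. Main estimate: RCC over all participants who had the abdominal CT, with its confidence interval.
2. T0 RCCs: report over all YLST participants who had a T0 LDCT (use the actual number scanned, not the approximate 6500 recruited), labelled a lower bound for partial kidney coverage. Alternatively, give them as case counts with stage and no proportion.
3. State that the mass-selected group is not used as a prevalence denominator and is not added to the abdominal-CT denominator.
4. If a combined first-screen figure is wanted, use d0/N0 + (1 − d0/N0) × d2/N2 with a confidence interval. Note that T0 coverage is partial, that the figure carries two years of incidence, and that it treats those scanned at T2 as representative of T0-screened people with no RCC detected.
5. In the stage table, put RCCs found only through lung-lesion staging on a separate line.

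The cost is a few sentences and the T0 scan count from YLST; no new data collection is needed. The drawback is that the T0 proportion becomes a lower bound and must be described as one.

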### Patient and public involvement

Two members of the public were involved in the design of this study and contributed to the research proposal prior to submission for funding. They have also commented on all participant facing documentation and continue to contribute to the study as members of the Independent Trial Steering Committee.

## Ethics and dissemination

This study was granted approval by the North West—Preston Research Ethics Committee (reference 21/NW/0021), and the Health Research Authority on 3 February 2021. It has been adopted onto the National Institute for Health Research trial portfolio (reference 290336). The University of Leeds is the sponsor and together with LTHT acts as joint data controller. The trial will have three committees providing oversight: the Trial Management Group (TMG), the Independent Data Monitoring Committee (IDMC) and an Independent Trials Steering Committee (TSC). The TMG will meet on a monthly basis, and will consist of the co-ordinating team based in Cambridge, members of the YKST team based in Leeds as well as the YLST principal investigator, data manager, project manager and lead nurse. The TMG will provide regular monitoring of the trial and provide clinical, scientific and practical advice. The IDMC will meet once or twice a year and will monitor patient safety as well as interim data. The TSC will meet once or twice a year and will provide overall oversight for the trial. The independent members of the IDMC and TSC will include experts in the field of cancer screening, radiology, renal cancer and statistics. The TSC will also include at least one patient/public representative.

Findings from the study will be reported in open-access papers in peer-reviewed journals and presented at national and international conferences. We will also provide a lay summary of the findings on the study website (www.YKST.org).

## Discussion

As the first study of its kind, YKST will assess the feasibility and acceptability of a combined abdominal and lung cancer screening approach and estimate other key uncertainties needed to inform a health economic analysis and future randomised controlled trials. Nesting YKST within an ongoing randomised lung cancer screening trial also provides a unique opportunity to generate the first cohort of participants invited to undergo screening for RCC. Although limited to assessing uptake and acceptability among participants who have already accepted screening for lung cancer and not large enough on its own to enable precise estimates of prevalence of RCC or an assessment of whether screening for RCC reduces RCC mortality, this cohort will be a valuable foundation for future research.
